##### Clinical assessments

The clinical measures include examination of CRPS signs and symptoms, sensory thresholds, autonomic changes, and motor functions. Participants with CRPS undergo all clinical assessments in RS1-RS4, whereas healthy control participants undergo the same clinical assessments during a single research session. Locations for sensory testing are the most painful site on the CRPS-affected limb and the corresponding site on the unaffected limb, always beginning with the unaffected limb so that participants can be familiarised with the test procedures and sensations before the tests are administered on their painful limb. For sensory testing in control participants, measures taken from the limb corresponding to the CRPS-affected limb of their matched participant with CRPS are compared to measures taken from the other limb.

CRPS diagnosis is confirmed in RS1 and RS2 during the baseline period, before commencement of the treatment, based on the Budapest research criteria [51]. These criteria are also assessed in the post-treatment period (RS3-RS4) to determine if the participants still meet the CRPS diagnosis.

The severity of symptoms is assessed and quantified as CRPS severity score in RS1-RS4, according to a recently validated protocol [35, 52]. Each of the 16 items is recorded as present (“1”) or absent (“0”) based on the self-reported symptoms and the signs confirmed at the time of examination through sensory testing, visual, and manual assessments. These include continuing, disproportionate pain; allodynia; hyperalgesia and/or hypoesthesia; temperature, colour, and sweating asymmetry; oedema; dystrophic changes; and motor abnormalities. Summed scores indicate the overall CRPS severity score. Where possible, criteria are evaluated based on a comparison between the affected and unaffected upper limb for a sign to be classified as present, including objective quantification of limb temperature asymmetry, oedema, muscle weakness, and active range of movement.

Photographs of the dorsal and palmar surface of both hands and forearms are taken so that the presence of skin colour and trophic changes can be double-scored by a researcher who is not involved in data collection and who is blind to the time point at which the photographs were taken, to which limb is affected by CRPS, and to which group the participant is allocated. Video recordings of both limbs performing the movements of fist closure and opening, wrist flexion and extension, and radial and ulnar wrist deviation are taken so that the motor abnormalities can be double-scored according to the same protocol. We will use Cohen’s kappa statistic to report inter-rater agreement.

An infrared thermometer is used to measure temperature asymmetry. Temperature measurements are taken to the nearest 0.1 °C from the dorsal and palmar surface of both hands (over the thenar muscle) and the centre of the region of worst pain as indicated by the participant. An arithmetic mean of the 3 measurements on each limb is calculated. According to the Budapest diagnostic criteria [51], an absolute difference between the affected and unaffected side greater than 1 °C is classed as a temperature asymmetry. When available, thermal images of both limbs are additionally taken (camera FLIR T620 that is sensitive to changes in temperature as small as 0.04 °C).

Oedema is measured using the figure-of-eight procedure that uses a soft tape measure. The detailed protocol for hand and wrist size measurement is described elsewhere [73]. This measure has excellent intra- and interrater reliability and concurrent validity compared with water volumetry [74]. Hand size is calculated as an arithmetic mean of 3 measurements performed on each hand. Presence of asymmetric oedema is considered if the average measure taken from the CRPS-affected hand is at least 0.56 cm larger compared to the unaffected hand, which was suggested to be a clinically relevant difference in a previous study [75].

Grip strength is measured as a marker of muscle weakness, using an electronic hand dynamometer (Constant, model 14,192-709E). Participants are seated in a chair with their elbows flexed at 90°, forearms in neutral position, and wrists at between 0 and 30° extension. They are instructed to squeeze the dynamometer’s handle as hard as they can and perform three such trials with each hand, alternating between the hands and allowing a pause of at least 15 s between each trial. An arithmetic mean of the 3 measurements (kg force) for each hand is calculated. Muscle weakness of the affected hand is indicated if the ratio of grip force in the affected to unaffected side is smaller than 0.95 for left-handed participants or smaller than 0.85 for right-handed participants. These criteria take into account the normal difference between dominant and non-dominant hands for left- and right-handed individuals [76, 77].

Active range of movement in the hands is assessed by measuring a change in Finger-To-Palm (∆FTP) distance (cm). A detailed measurement protocol is described elsewhere [78]. ∆FTP is an index of the extent to which a person can fully flex their fingers (e.g., to make a fist) relative to the extent to which they can extend them (e.g., to make their hand flat). ∆FTP was selected as a measure of range of movement as it takes into account both these aspects of motor function, unlike classic FTP that only regards the maximum flexion. A significant decrease in the range of movement in the affected hand is defined as ∆FTP_affected_ / ∆FTP_unaffected_ < 0.9.

In addition to those limb differences that are assessed through clinical examination for the CRPS severity score, differences between the affected and unaffected limbs are also objectively quantified through elements of a standard Quantitative Sensory Testing (QST) procedure to assess hypoesthesia, pinprick hyperalgesia, and allodynia. Participants undergo the assessment of Mechanical Detection Threshold (MDT) that follows the standardized protocol [79] using von Frey filaments of 0.008 g to 300 g force (Bioseb, model Bio-VF-M). Then the ratio of thresholds for affected vs. unaffected side is derived [(MDT_affected_-MDT_unaffected_)/MDT_affected_]. A positive score indicates hypoesthesia (increased tactile detection threshold) on the affected side. Based on relative QST reference data comparing both sides of the body, hypoesthesia is confirmed if the ratio is ≥0.38 [80]. We also assess Mechanical Pain Threshold (MPT) according to the standardized protocol [79] on both limbs, using pinprick stimulators of 8mN to 512mN intensities (MRC Systems PinPrick Stimulator Set). A positive thresholds ratio [(MPT_unaffected_-MPT_affected_)/MPT_unaffected_] indicates hyperalgesia (decreased pain threshold) on the affected side. Hyperalgesia is confirmed if the ratio is ≥0.4, based on relative QST reference data comparing both sides of the body [80]. Allodynia is examined using a procedure adapted from the dynamical mechanical allodynia test of the QST [79]: the cotton ball, Q-tip and brush (MRC Systems PinPrick Stimulator Set) are applied to the skin five times each, in a random order, with a single 1-2 cm long sweeping motion lasting approximately 1 s. Participants rate each sensation on a scale from 0 – “no pain, no sharp, pricking, stinging, or burning sensation” to 100 – “most intense pain sensation imaginable”. Any sharp, pricking, stinging, or burning sensation is defined as painful and given a rating above 0. Allodynia is quantified as an arithmetic mean of 15 ratings on each limb. Its presence is indicated by scores greater than zero.

A Two-Point Discriminator disk (Exacta, North Coast Medical) is used to record tactile discrimination thresholds [53]. The participant’s index finger tip is touched either with one tip or two tips of the disk for 3 s per touch, with consistent pressure, and while the participant has their eyes closed. On each trial, participant reports whether they perceived touch on one point or two points of their finger. The procedure starts with two points separated by 7 mm distance, and the distance between points is increased or decreased (down to a single tip) across trials according to the staircase procedure. For example, if the participant initially reports two touches, smaller distances are applied until the participant reports the sensation of only one point. The distance is then increased until a sensation on two points is reported again. The procedure continues until 5 subthreshold and 5 suprathreshold values are obtained. The tactile discrimination index is calculated as a geometric mean of these 10 turning points for each hand. To quantify the difference between the two sides of the body, we derive the tactile discrimination thresholds ratio [(affected-unaffected)/affected]. Positive score indicates less precise tactile discrimination ability on the affected limb.

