### Participants

#### Eligibility criteria

##### Participants with CRPS

This study enrols both male and female individuals, who:
are willing and able to give informed consent to take part in the trial,are aged 18–80,have a diagnosis of CRPS type I based on the Budapest diagnostic research criteria [2] as assessed at RS1 and revisited at RS2,have CRPS type I primarily affecting one upper limb,have had CRPS for a minimum of 3 months at the time of RS1,and report current pain intensity ≥2 on a 0–10 Numeric Rating Scale at RS1 and RS2.

Participants are excluded from the CRPS group if they:
lack sufficient English language ability to provide informed consent,are classified as legally blind,have a history of neurological disorder (e.g. stroke, neurodegenerative disease or traumatic brain injury),have CRPS meeting the Budapest diagnostic clinical or research criteria affecting both sides of the body,^2^report that they have confirmed presence of nerve damage (CRPS type II) based on the results of nerve conduction test,have dystonia or any other physical limitation severe enough to prevent satisfactory execution of PA/sham treatment,or have a severe psychiatric comorbidity (such as schizophrenia) that in the researchers’ opinions would compromise participation in the study.

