### Randomisation

Treatment allocation is conducted by method of randomisation with stratification to minimise baseline (RS1) group differences. Eligible participants with CRPS are allocated in equal numbers to one of the two treatment groups: PA treatment group or sham treatment group. Group allocation is performed using MINIM computer programme [34] by a researcher who is not involved in data collection ([name]). The minimisation procedure controls for the stratification factors that are listed in Table 2. In the event of participant’s withdrawal after treatment allocation, but before RS3, their data shall be removed from the minimisation procedure and an additional participant shall be recruited for the trial to ensure equal numbers of full datasets with any post-intervention data in the two groups.

**Table 2 Tab2:** Criteria for stratification as recorded in RS1

Factor	Weight	Categories
Current pain intensity (0–10 Numerical Rating Scale)	2	≤ 6
		> 6
CRPS severity score (1–16) [35]	2	≤ 12
		> 12
Primarily affected arm	1	Left
		Right
Pre-CRPS dominant hand (writing)	1	Left
		Right
Sex	1	Male
		Female
Age	1	18 - < 40
		40 - < 61
		61–80
Presence of CRPS in body parts other than the primary affected arm	1	Yes
		No
Presence of other non-CRPS pain	1	Yes
		No
CRPS duration	1	< 1 year
		1 - < 5 years
		5 - < 10 years
		≥ 10 years

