#### Primary outcomes

A change between RS2 (immediately before the commencement of treatment) and RS3 (immediately after the end of the treatment period) in current self-reported pain intensity and CRPS severity score [35, 52] are the primary outcomes. People with CRPS consider pain relief to be the highest priority for recovery [59], and pain intensity is the most common primary outcome in chronic pain trials [60]. Current pain intensity is measured using item 6 of the Brief Pain Inventory (BPI; short form) [42], which is a Numerical Rating Scale (NRS) ranging from 0 – “no pain” to 10 – “pain as bad as you can imagine”. The BPI has high reliability [42]. In addition to pain, CRPS involves a range of other debilitating symptoms, some of which were also affected by PA in previous studies [22, 24]. Therefore, we included a comprehensive measure of symptoms severity as the second primary outcome. The CRPS severity score assessment protocol follows the 16-points scoring system published by Harden and colleagues [35]. This continuous index of CRPS symptom severity has good discrimination abilities, concurrent validity and adequate sensitivity to change [35, 52], and has been recommended as one of the core outcome measures for CRPS clinical studies [61].

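### The grip-weakness cut-off is set by handedness alone, so it allows for the normal difference between hands only when the non-dominant hand is affected

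*Protocol article*

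**What the plan says.** Under Clinical assessments, grip force is averaged over three trials per hand. The criterion for a weak affected hand reads: "ratio of grip force in the affected to unaffected side is smaller than 0.95 for left-handed participants or smaller than 0.85 for right-handed participants". The justification follows at once: "These criteria take into account the normal difference between dominant and non-dominant hands for left- and right-handed individuals". The rule does not depend on which hand is affected.

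The result feeds the CRPS severity score. Its 16 items are each scored 0 or 1, and signs are judged where possible by comparing the two upper limbs, "including objective quantification of limb temperature asymmetry, oedema, muscle weakness, and active range of movement". The Primary outcomes section states that the RS2 to RS3 changes "in current self-reported pain intensity and CRPS severity score [35, 52] are the primary outcomes".

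Either arm may be affected. The eligibility criterion is to "have CRPS type I primarily affecting one upper limb", without regard to dominance. Table 2 under Randomisation records both the "Primarily affected arm" and the pre-CRPS writing hand, each as left or right.

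**The concern.** The ratio is affected over unaffected, whereas the allowance it is meant to contain concerns dominant versus non-dominant. The two line up in one direction only. If the non-dominant hand is affected, a healthy ratio is somewhat below 1, and a cut-off below 1 makes room for that. If the dominant hand is affected, a healthy ratio is above 1, and the same cut-off demands a larger loss before weakness is recorded.

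Within a certain band, therefore, the same proportional loss is a present sign in one participant and an absent sign in another, depending only on which hand is affected. The analysed quantity is change from RS2 to RS3, so the two kinds of participant also register improvement at different degrees of recovery.

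**Working it through.** **Inputs.** The cut-offs are c = 0.85 (right-handed) and c = 0.95 (left-handed), from Clinical assessments. They rest on cited reference data and cannot be reproduced from the protocol. Let g be the normal ratio of non-dominant to dominant grip. The protocol does not give g, so the values below are assumptions: 0.85 to 1.00 for right-handers and 0.95 to 1.00 for left-handers. Let L be the proportional loss in the affected hand.

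**Formulas.**
- Non-dominant hand affected: ratio = g(1 − L), so weakness is scored when L > 1 − c/g.
- Dominant hand affected: ratio = (1 − L)/g, so weakness is scored when L > 1 − c·g.

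The two limits coincide only if g = 1. That would mean no normal difference between hands, contrary to the protocol's own justification. The direction of the problem therefore needs no outside figure; only its size does.

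**Loss above which weakness is scored.**

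| Handedness (c) | g | Non-dominant affected | Dominant affected |
|---|---|---|---|
| Right (0.85) | 0.95 | 1 − 0.85/0.95 = 10.5% | 1 − 0.85×0.95 = 19.3% |
| Right (0.85) | 0.90 | 1 − 0.85/0.90 = 5.6% | 1 − 0.85×0.90 = 23.5% |
| Right (0.85) | 0.85 | 1 − 0.85/0.85 = 0% | 1 − 0.85×0.85 = 27.8% |
| Right (0.85) | 1.00 | 15% | 15% |
| Left (0.95) | 0.97 | 1 − 0.95/0.97 = 2.1% | 1 − 0.95×0.97 = 7.9% |
| Left (0.95) | 0.95 | 0% | 1 − 0.95×0.95 = 9.8% |
| Left (0.95) | 1.00 | 5% | 5% |

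**Scoring at one visit (right-hander, g = 0.90).** A 20% loss in the right hand gives 0.80/0.90 = 0.889, scored as no weakness. The same loss in the left hand gives 0.90×0.80 = 0.720, scored as weakness. At a 30% loss the ratios are 0.778 and 0.630, and both are scored as weakness.

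**Scoring of change (same assumption).**
- Recovery from a 30% to a 10% loss: a dominant hand goes from 0.778 to 1.000, present to absent, and gains a point. A non-dominant hand goes from 0.630 to 0.810, present both times, and gains nothing.
- Full recovery from a 20% loss: a dominant hand goes from 0.889 to 1.111, absent both times. A non-dominant hand goes from 0.720 to 0.900, present to absent.

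Sensitivity to change thus differs by side, but neither side is always the less sensitive one.

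**The case against.** The best defence is that little of this reaches the primary result. Weakness is one contributor to the motor signs. Range of movement has its own cut-off, and motor abnormalities are also double-scored from video, so the item will often be decided elsewhere. About one point is the most that can be affected, against the 4.9-point reduction that the protocol treats as clinically significant. Losses beyond the upper limit are scored alike in both hands. The size depends on a normal ratio that the protocol does not give: at g = 0.90 the two limits differ about fourfold (23.5/5.6), at g = 0.95 less than twofold (19.3/10.5). The cut-offs do differ by handedness and do allow for a weaker non-dominant hand, so the stated justification is incomplete rather than empty. All of this stands, and it limits the point. It does not remove it, because no other part of the protocol ties the cut-off to the affected side.

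Three stronger readings are tempting and not supported:
- **Bias between the groups.** Affected side and pre-CRPS dominance are fixed within a person, the outcome is within-person change, and both are minimisation factors, though separate ones. Nothing shows that the arms would be affected differently.
- **Weakness in a dominant hand generally missed and unable to improve.** This holds only for losses below the upper limit where no other motor sign is present.
- **Disturbed trial entry through the Budapest criteria.** The article does not set out the motor component of those criteria, so it gives no basis for this.

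**Conclusion.** The point holds in a limited form. As written, the cut-off makes the allowance it claims only when the non-dominant hand is affected. For right-handers, under an assumed normal difference of 5% to 15%, losses from 10.5% to 19.3% at the narrow end, and from 0% to 27.8% at the wide end, are scored differently by side. Left-handers show the same pattern on a smaller scale.

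The consequence is misclassification and unequal sensitivity to change in at most about one point of a primary score, among participants whose motor item rests on grip. How many participants that is cannot be determined from the protocol. The grip-strength secondary outcome is analysed as a continuous ratio and does not use the cut-off, so it is unaffected. The rule is worth correcting because it is fully stated, enters a primary outcome and is cheap to repair.

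**What to change.** 1. Divide the observed affected/unaffected ratio by the normal ratio for that participant's handedness and affected side: g if the non-dominant hand is affected, 1/g if the dominant hand is. Take g from the reference data already cited. Both cases then reduce to the same quantity, since g(1 − L)/g = 1 − L and [(1 − L)/g]/(1/g) = 1 − L.
2. Apply one proportional-loss threshold to all participants whichever hand is affected, justified from the same reference data and fixed before any re-scoring. Carrying the present cut-offs over would not do this: at g = 0.90 the 0.85 limit is only a 5.6% loss in a non-dominant hand, so near-normal grip can count as weak.
3. State that handedness here means pre-CRPS dominance. Baseline descriptors collects both current and recalled preference, and the grip rule does not say which applies.
4. Re-score the weakness sign at RS1 to RS4 from the kg-force values before the assessor is unblinded. Report how many severity scores change, and keep the protocol's present scoring as a sensitivity analysis.

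The cost is a short amendment to the scoring rule and a mechanical recalculation. Grip force, affected arm and pre-CRPS dominant hand are already collected, so no new measurement is needed. The downside is that a few severity scores will change. Some of these may be RS1 scores already used in minimisation; those allocations stand.

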##### Computer-based/psychophysical tests

Six computer-based measures are used in the present study to assess the following neuropsychological functions: visuospatial attention, cognitive representation of space, spatially-defined motor function, and body representation. To test for spatial attention bias in near space, we administer versions of three tasks that have been used to measure spatial attention in hemispatial neglect: a visual Temporal Order Judgement (TOJ) task [8], a Landmark task [54], and a Greyscales task [55]. The fourth task is a Mental Number Line Bisection task, which measures the mental representation of space [56, 81]. The fifth task is a Directional Hypokinesia task, a measure of motor “neglect-like” impairment. The final computer-based task is a Hand Laterality Recognition task, which is thought to be indicative of body representation [58].

All measures presented in this section are collected in RS1-RS4 from the participants with CRPS and during a single research session from healthy control participants. Hand and side of space for all tasks are coded as affected or unaffected (for controls, the “affected” and “unaffected” hand / side is coded based on their matched participant with CRPS). Each task is preceded by a short practice session to familiarise the participant with the task. If they do not appear to follow the instructions during practice, these are explained again, and the practice is repeated.

***Visuospatial attention*** The following three computer-based tests are used to measure visuospatial attention: the visual TOJ task, the Landmark task and the Greyscales task.

*The visual TOJ task* TOJ tasks are sensitive measures of covert spatial attention, used both in clinical populations [82–88] and healthy people [89–93]. The usual procedure involves presenting pairs of identical stimuli, one on each side of space, with different onsets but the same duration. The participant’s task is to report which of the two stimuli they perceived first. According to the prior entry hypothesis [94], stimuli that are subject to greater attention are perceived earlier relative to stimuli that are subject to lesser attention. The TOJ task takes advantage of this premise. The visual variant of the TOJ used in this study is similar to that described in a previous article [8]. The participants keep their hands uncrossed on their laps under the table, and have their head stabilised by a chinrest. They are instructed to maintain their gaze on a black fixation point (3 mm in diameter), approximately 28 cm from their torso, located in the centre of a 46.5 × 35.5 cm white board laid on a table. Pairs of brief (10 ms) red light stimuli (3 mm in diameter) are presented using laser pointers controlled via an Arduino platform that is integrated with PsychoPy software [95]. The lights are presented 9 cm (approximately 18°) to the left and 9 cm to the right of the fixation point (one on each side), using a range of ten temporal offsets: ±10, ±30, ±60, ±120 and ± 240 ms (with negative numbers representing the trials in which the light on the affected side appeared first). Each temporal offset is presented 15 times in pseudorandom order, giving a total of 150 trials. To account for any response bias [96] the participants complete the TOJ task once while indicating which of the two lights appeared first, and a second time while indicating which light appeared second (order counterbalanced between participants). Participants’ verbal responses (“Left” or “Right”) are inputted via the computer keyboard by the researcher. The relative number of left-right responses to different offsets of the stimuli is re-expressed as the number of affected-unaffected responses. To derive the Point of Subjective Simultaneity (PSS) for each participant and each condition, these data are then fitted with a cumulative Gaussian using a criterion of maximum likelihood. The PSS expresses the amount of time (ms) by which the light that appears in the affected side of space should precede (negative PSS values) or follow (positive PSS values) the light that appears in the unaffected side of space for the two stimuli to be perceived as simultaneous. For the analysis, PSSs from the two response blocks (which light appeared first or second) will be averaged to obtain a single index of attention bias. A negative PSS value indicates a bias of attention away from the affected side, whereas a PSS value of 0 indicates equal distribution of attention to both sides of space.

*The landmark task* In addition to the TOJ task, participants complete four tasks involving presentation of visual stimuli on a computer screen. For these, participants are seated with their head in a chinrest that is aligned with the centre of the screen. Stimuli are presented on a laptop touch screen (34.5 cm × 19.4 cm size, 1920 × 1080 pixels resolution) using PsychoPy software [95] on the Windows 10 operating system. The laptop screen is positioned at a viewing distance of 50 cm. The responses are recorded using a custom-made button box positioned such that the buttons are aligned vertically.

We use a modified version of a Landmark task to measure bias in attention to or the representation of relative horizontal distance in near space. The task is adapted from a previous study [54] and involves simultaneous presentation of two stimuli (“landmarks”; white circles 1.1° in diameter) to the left and to the right of a central fixation cross. The total distance between the two landmarks is kept constant across trials (15°), however, their position relative to the fixation cross varies by 0.1° increments from ±8.1° to ±6.9° away from the fixation cross in the horizontal plane (Fig. 1). Thus, there are 6 stimulus pairs in which the right landmark is closer to the fixation cross, 6 stimulus pairs in which the left landmark is closer, and 1 stimulus pair in which the distance of both landmarks from the fixation cross is equal. Each stimulus pair is presented 15 times during one block resulting in 195 trials per block, presented in pseudorandom order. The participant is instructed to maintain their gaze on a white, 1.4° high fixation cross presented in the centre of a grey screen. After 500 ms, the fixation cross is joined by the two stimuli which are displayed for 300 ms. Then a 200 ms mask is presented, consisting of a white 1.6° high line extending horizontally across the entire screen, with a grey fixation cross in the same location as the previous white one (Fig. 2).

